# Effects of a transitional palliative care model on patients with end-stage heart failure: study protocol for a randomized controlled trial

**DOI:** 10.1186/s13063-016-1303-7

**Published:** 2016-03-31

**Keywords:** Transitional care, Palliative care, End-stage heart failure, Health services utilization, Quality of life

## Abstract

**Background:**

Heart failure (HF) is characterized by high rates of readmission after hospitalization, and readmission is a major contributor to healthcare costs. The transitional care model has proven efficacy in reducing the readmission rate and economic outcomes, and increasing satisfaction with care. However, the effectiveness of the transitional care model has not been evaluated in patients with end-stage HF. This study was designed to compare the customary hospital-based care and a comprehensive transitional care model, namely the Home-based Palliative HF Program (HPHP), in terms of readmission rate, quality of life, and satisfaction with care among end-stage HF patients under palliative care.

**Methods/design:**

This is a randomized controlled trial taking place in hospitals in Hong Kong. We have been recruiting patients with end-stage HF who are identified as appropriate for palliative care during hospitalization, on referral by their physicians. A set of questionnaires is collected from each participant upon discharge. Participants are randomized to receive usual care (customary hospital-based care) or the intervention (HPHP). The HPHP will be implemented for up to 12 months. Outcome measures will be performed at 1, 3, 6, and 12 months post-discharge. The primary outcome of this study is quality of life measured by the Chronic Heart Failure Questionnaire - Chinese version; secondary outcomes include readmission rate, symptom intensity, functional status, and satisfaction with care.

**Discussion:**

This study is original and will provide important information for service development in the area of palliative care. The introduction of palliative care to end-stage organ failure patients is new and has received increasing attention worldwide in the last decade. This study adopts the randomized controlled trial, a vigorous research design, to establish scientific evidence in exploring the best model for end-stage HF patients receiving palliative care.

**Trial registration:**

This trial was registered as NCT02086305 on 7 March 2014 in the United States Clinical Trials Registration, and in the Clinical Trials Registry, Hong Kong University with the trial number UW12202.

**Electronic supplementary material:**

The online version of this article (doi:10.1186/s13063-016-1303-7) contains supplementary material, which is available to authorized users.

## Background

Heart failure (HF) is a global health issue affecting more than 5 million people in the United States (US) [1] and 14 million Europeans [2]. In Hong Kong, the overall HF ratio per 1,000 people is 0.7, resulting in a total of over 5,000 cases; the new:old case ratio is 2.8:1 [3]. Heart failure is the leading cause of death in the US, accounting for 31.4 % of all deaths and followed by cancer and stroke [4]. In Hong Kong, cancer is still the leading cause of death (30.6 %), but heart disease was ranked second (15.5 %) among the 42,705 deaths in 2009 [5]. The management of HF in recent years has improved, but the mortality rate remains high, with a reported 40 % death rate within the first year after diagnosis [6, 7] and 75 % at five years [8]. Patients with heart failure tend to need more emergency room visits, repeated hospital admissions, and longer lengths of stay [1]. In Hong Kong, around 25–50 % of HF patients are readmitted within 6 months of discharge [9]. The repeated use of services results in increased healthcare expenditures [10, 11], costing US$30 billion a year in the US [1] and GBP 905 million in the United Kingdom [8].

The prognosis for patients with HF is poor, and various burdens become prominent when HF progresses to the end stage. End-stage heart failure is resistant to medical therapy [1], and this group of patients experiences a marked reduction in health-related quality of life [6, 12], encountering health problems encompassing physical, psychological, social, and spiritual aspects. Topping the list of physical symptoms are fatigue, dyspnea, and edema [6, 12, 13]. Other reported symptoms include decreased appetite, cough, dry mouth, and pain [6, 12]. With their progressive decline in functional status, these patients often have increasing difficulty dealing with daily activities [14, 15]. Psychologically, some patients with HF live in the shadow of fear [16], experiencing emotional turbulence [17] and feeling frustrated with their sense of personal failure [18]. Patients show symptoms of insomnia, worry, sadness, and irritability [6, 12]. Socially, patients with HF feel isolated and lonely [14, 19–21], often relying on others for daily living assistance and thus regarding themselves as a burden to their carers [19]. These patients also face spiritual issues, such as questioning the meaning of living with severe HF as they experience strong feelings of uncertainty and hopelessness [20]. In fact, patients understand that their condition could change rapidly, including a sudden decline resulting in death [20, 22]. Apart from the symptom burden, heart failure also imposes a financial burden on the healthcare system, particularly in the form of hospital readmission [23, 24]. Heart failure is a leading cause of hospitalization, and a systematic review confirmed that about 25 % of patients hospitalized with HF are readmitted within 30 days [23]. Reasons for hospital readmission were worsening of symptoms, unavoidable progression of illness, distressing psychosocial issues, inadequate self-care adherence, and lack of knowledge on how to seek help from the healthcare provider [24, 25]. Therefore, it is essential to address end-stage HF patients’ physical, psychological, and spiritual needs in order to facilitate a better hospital-to-home transition for them.

Patients with heart failure suffer from a number of symptoms that profoundly impact their quality of life (QoL) towards the end of life [1, 26]. They share similar symptoms with patients who have cancer, including breathlessness, fatigue, and edema [27–29]. QoL concerns are also shared by cancer and non-cancer patients, both of whom may benefit from a palliative approach to their care [30, 31]. Traditional medical practice tends to focus almost exclusively on curing illness and prolonging life while treating advanced illnesses, rather than on improving QoL and relieving suffering [32]. Contemporary trends in the treatment of heart failure advocate the integration of palliative care into comprehensive heart failure management [33, 34]. Regarding the extensive healthcare concerns raised during end-stage HF, recent literature and guidelines indicate that the provision of palliative care (PC) for end-stage HF patients is important. The American College of Cardiology and American Heart Association Guidelines [35], the Heart Failure Association of the European Society for Cardiology [36], the Canadian Cardiovascular Society [37], and the Hong Kong College of Physicians [38] all state that a palliative approach to care for patients with end-stage HF should be adopted.

Palliative care has a long history among patients with cancer, and the evidence in palliative care research is substantial [39]. In recent years, although it has become clear that palliative care can also benefit non-cancer patients, a systematic review looking at the effectiveness of specialized palliative care concluded that evidence of the benefits of this kind of care is sparse. Some authors have recommended carefully planned trials using a standardized palliative care intervention for terminally ill patients [40]. Specialized intervention [41] and coordination of care for patients with end-stage HF is needed to help reduce the risk of care fragmentation and to improve communication when many health professionals are involved [36].

Therefore, we designed the present study aiming to compare the effects of customary hospital-based care and an interventional Home-based Palliative HF Program (HPHP). Our objective is to examine the effect of the HPHP on hospital readmission rate, quality of life, functional status, symptom intensity, and satisfaction with care. The key outcome of this study is the hospital readmission rate, and the primary endpoint is 4 weeks post-discharge. The hypothesis is that patients with end-stage heart failure (ESHF) receiving the HPHP will have a lower hospital readmission rate than those receiving customary hospital-based care at 4 weeks post-discharge.

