### Primary outcome

The primary outcome is quality of life, which will be measured by an HF-specific scale, the Chronic Heart Failure Questionnaire - Chinese version (CHQ) at 4 weeks post-discharge. The CHQ is one of the most commonly used HF-specific QOL instruments. It was developed by Guyatt et al. [58] in Canada. The tool has 20 items on a 7-point Likert scale measuring four domains: dyspnea, fatigue, emotional status, and mastery. The CHQ has been translated into Chinese and validated [59]. The internal consistency and test-retest reliability are good, with a Cronbach’s alpha of 0.95 and an intra-class correlation coefficient (ICC) of 0.75 [59]. In addition, the quality of life will also be measured by the McGill Quality of Life Questionnaire - Hong Kong version (MQOL-HK), which is a palliative-specific instrument measuring four domains: physical, psychological, existential, and support on a numerical scale from 0 to 10. It has been validated among palliative patients in Hong Kong with good reliability (the ICC is 0.85 (*p* < 0.0001) and the Cronbach’s alpha is 0.83) [60].

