### Secondary outcomes

Evaluated health outcomes will be functional status, symptom intensity, and satisfaction with care. Functional status will be measured by the Palliative Performance Scale (PPS). The PPS, developed by Anderson et al. [61] based on the Karnofsky Performance Scale, is a tool specifically designed for palliative patients that reflects the changing physical condition in five aspects: ambulation, activities/evidence of disease, self-care, intake, and level of consciousness. The PPS is a clinical tool commonly used in local settings. The level of physical performance is rated on a scale of 100 (normal) to 0 (death), measured in 10 % decrement levels. The scale has been validated and the inter-rater reliability between doctors and nurses was maintained at .85 with strong kappa values of .97 [62]. The internal consistency is also good, with a Cronbach’s alpha equal to 0.83 [63].

The symptom intensity will be measured by the Edmonton Symptom Assessment System (ESAS). The ESAS assesses nine symptoms: pain, fatigue, nausea, depression, anxiety, drowsiness, appetite, sensation of well-being, and dyspnea, measured on a 0–100 mm visual analog scale (VAS). One extra empty VAS is left for the assessment of a less frequent symptom that may be important for an individual patient. The ESAS is widely adopted locally, and has been found to be a valid, reliable instrument for use among palliative care patients [64, 65]. A local study has also shown that the ESAS can help quantify symptoms and is an independent prognosticator for survival [66].

Satisfaction with care will be measured by the 15-item questionnaire used in the study of Wong et al., with validity confirmed by an expert panel and a reported test-retest reliability of .87 [42].

The service utilization outcome is measured by the hospital readmission rate, length of stay, and emergency room visits. The information will be extracted from the hospital administrative systems.

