### Statistical methods

#### Sample size estimation

We estimated the sample size based on the study by Brannstrom and Boman [67], which detected a significant improvement in quality of life (intervention 60.4 versus control 52.3) after the structured palliative home care intervention provided by a multidisciplinary team among heart failure patients. A sample size of 117 for each arm is required to achieve a power of 80 % at a significance level of 0.05. To account for a 20 % attrition rate, 140 subjects for each arm with a total of 280 subjects are needed.

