### Data analysis

We will use SPSS 22.0 for Windows to perform a statistical analysis. Descriptive statistics and means will be used to describe the participants’ background information and clinical variables. Poisson regression will be used to examine the mean difference for the hospital readmission rate between groups. A generalized estimating equation (GEE) will be used to examine the group, time, and interaction effects on the secondary outcome variables. The GEE is chosen because it treats observations of longitudinal data as correlated and thus is more robust in estimating standard errors [68].

The final report will follow the Consolidated Standards of Reporting Trials (CONSORT) statement as well as its extension for non-pharmacological interventions/complex intervention.

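### The protocol gives the confirmatory role to readmission in its hypothesis and to CHQ quality of life in its outcome and sample size sections, and the stated 80% power covers only quality of life

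*Protocol article*

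**What the plan says.** Two sections of the protocol article put readmission first.

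- **Background, last paragraph:** "The key outcome of this study is the hospital readmission rate, and the primary endpoint is 4 weeks post-discharge". The hypothesis that follows is that patients on the home-based programme "will have a lower hospital readmission rate than those receiving customary hospital-based care at 4 weeks post-discharge". No hypothesis is stated for quality of life.
- **Data analysis:** "Poisson regression will be used to examine the mean difference for the hospital readmission rate between groups". Generalized estimating equations (GEE) are then assigned to the outcomes that the section calls secondary.

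Four places put quality of life first or readmission second.

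- **Abstract, Methods/design:** "The primary outcome of this study is quality of life measured by the Chronic Heart Failure Questionnaire - Chinese version", and "secondary outcomes include readmission rate, symptom intensity, functional status, and satisfaction with care".
- **Primary outcome:** "The primary outcome is quality of life, which will be measured by an HF-specific scale", the CHQ, at 4 weeks after discharge.
- **Secondary outcomes:** readmission appears here, under service use: "The service utilization outcome is measured by the hospital readmission rate, length of stay, and emergency room visits".
- **Sample size estimation:** the calculation starts from an earlier study "which detected a significant improvement in quality of life (intervention 60.4 versus control 52.3"). It gives 117 per arm for 80% power at 0.05, then 140 per arm after attrition. It contains no readmission rate.

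No section splits alpha between the two outcomes or sets an order of testing.

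**The concern.** A protocol should let a reader say which single result decides the trial. Here the objective, the hypothesis and the layout of the analysis point to readmission. The abstract, the outcome sections and the sample size point to the CHQ. These are opposing statements in the current text, and condensing a longer protocol into an article does not explain them.

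Two things are at stake. First, either result could be reported as the prespecified one with some support from the text, and the nominal 5% error rate would not then describe the headline claim. Second, a reader who takes the hypothesis at face value would credit it with 80% power that was never calculated for it. The Trial status section puts the study at the final stage of data collection, so little time remains to settle the matter before outcomes are analysed by allocation.

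**Working it through.** **Step 1. Which outcome each section favours**

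| Section | Readmission | CHQ quality of life |
|---|---|---|
| Abstract | secondary | primary |
| Background | key outcome, sole hypothesis, 4 weeks | no hypothesis |
| Primary / Secondary outcomes | secondary | primary, 4 weeks |
| Sample size estimation | no input | sole basis |
| Data analysis | separate from the secondary outcomes | no analysis assigned to it as primary |

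The two sides agree only on the time point.

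**Step 2. The plan's own figure**

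Inputs from Sample size estimation: difference 60.4 − 52.3 = 8.1, power 80%, alpha 0.05, 117 per arm. No standard deviation is given, so 117 cannot be reproduced, only solved backwards (two-sided):

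SD = 8.1 × √(117/2) / (1.960 + 0.842) ≈ 22.1, a standardised difference of about 0.37.

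The figure is therefore plausible for a quality-of-life score. No readmission quantity enters it.

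**Step 3. Type I error if success on either outcome could be claimed**

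- Independent tests: 1 − 0.95² = 0.0975.
- Correlated test statistics (bivariate normal, two-sided 0.05 each): 0.095 at correlation 0.3, 0.091 at 0.5 and 0.083 at 0.7.

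**Step 4. Power for readmission under the planned Poisson comparison**

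The protocol gives no control rate for this trial. The nearest figure is in the Background: about 25% of patients hospitalised with heart failure are readmitted within 30 days. I take 0.25 as an assumed control mean, with 0.35 and 0.50 as further assumed values. For a Wald test on the log rate ratio R with n per arm and control mean m:

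SE = √(1/(n·m) + 1/(n·m·R)), power = Φ(|ln R|/SE − 1.96).

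With n = 140 and m = 0.25, the expected control count is 35.

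- R = 0.75: SE = √(1/35 + 1/26.25) = 0.258; |ln 0.75| = 0.288; power = Φ(1.114 − 1.96) = Φ(−0.846) ≈ 0.20.
- R = 0.42: SE = √(1/35 + 1/14.7) = 0.311; |ln 0.42| = 0.868; power = Φ(2.79 − 1.96) = Φ(0.83) ≈ 0.80.

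| Assumed control mean | Power at R = 0.75, 140 per arm | R for 80% power, 140 per arm |
|---|---|---|
| 0.25 | 0.20 | 0.42 |
| 0.35 | 0.26 | 0.50 |
| 0.50 | 0.35 | 0.57 |

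These figures assume 4 weeks of follow-up on all 140 per arm and no overdispersion, so they lean towards optimism. With 112 per arm (20% lost) and a mean of 0.25, the rate ratio for 80% power is about 0.36.

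**The case against.** **The labels are not literally identical.** The words primary outcome are attached only to quality of life. The Background speaks of a key outcome, and its primary endpoint is a time point that the CHQ shares. That is true, and it is a good reason to resolve the conflict in favour of the CHQ. It does not remove the conflict, because the same paragraph states the only hypothesis on readmission.

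**The analysis split may be by data type.** Poisson regression for a count and GEE for repeated scores is a natural division, and Data analysis never calls readmission primary. This stands in part. The exact CHQ contrast may be left to an analysis plan, so its absence is not the complaint. What remains is a mislabel: the GEE is given to secondary outcomes while the declared primary outcome is a repeated score.

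**A reader might infer that the confirmatory test was left open to be picked after seeing the data.** The documents do not support that. Nothing in them permits a claim on either outcome or suggests switching. Registration in March 2014 is reported, but that record is not at hand and may have settled the choice. The 9.75% is an upper figure that needs both an either-outcome claim and independent tests.

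**A reader might also state a fixed detectable difference for readmission,** such as 25% against about 12%, which is what a two-proportion test gives at 140 per arm. That is not the planned test. The 25% also comes from a review of heart failure patients generally, and the Discussion says that review's results may not carry over to the severely ill. Only a range is defensible.

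**Conclusion.** The contradiction is real and concerns what the trial's confirmatory claim is. It must be resolved, although the remedy is only wording.

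Three conclusions follow.

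- The 80% power belongs to quality of life and not to the only hypothesis stated. This follows from the text and needs no assumption.
- If either outcome could carry the claim at 0.05, the type I error would be about 8% to 9.75% for correlations from 0.7 down to 0. This is conditional on a reading that the text leaves possible but does not endorse.
- Readmission would probably be underpowered for moderate effects: 20% to 35% power for a 25% reduction at 140 per arm, over assumed control means of 0.25 to 0.50. A large effect could still be detected, at a rate ratio near 0.42 for a mean of 0.25 and near 0.57 for a mean of 0.50.

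**What to change.** Before outcomes are analysed by allocation:

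1. Declare the CHQ at 4 weeks the single primary outcome. This agrees with the abstract, the Primary outcome section and the sample size, and leaves alpha and the planned numbers unchanged.
2. Rewrite the objective and hypothesis in the Background for the CHQ at 4 weeks.
3. Label readmission secondary throughout.
4. In Data analysis, name the 4-week CHQ group comparison from the GEE as the primary analysis. Keep Poisson regression for readmission as a secondary analysis.

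If the sponsor prefers to keep readmission as key, say in Sample size estimation that the 80% power does not apply to it. Give its detectable rate ratio under the planned Poisson model over a range of assumed control rates, rather than one pair of percentages. The abstract and both outcome sections must then be changed to match.

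The cost is a wording amendment. The downside of the recommended route is that readmission loses confirmatory status.

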## Methods/design

### Overview of study design

This is a two-group, single-blinded randomized controlled trial. Participants are randomly allocated to two groups: the customary hospital-based (control) group and the HPHP (intervention) group. Eligible participants will be recruited from three regional hospitals in Hong Kong. The Standard Protocol Items: Recommendations for Interventional Trials (SPIRIT) guidelines for the trial are presented in Additional file 1.

### Preparatory phase

The preparatory phase includes the development of evidenced-based intervention protocols (6 months) and a training program for service providers (6 months).

### Trial phase

This study (that is, the baseline assessment of subjects and intervention implementation for up to 12 months) will take 12 months. Intervention effects will be measured at 1 month, 3 months, 6 months, and 12 months and compared with the baseline measurements, as well as between the HPHP and control groups (Fig. 1).

**Fig. 1 Fig1:**
[figure not shown]
Flowchart for transition palliative care trial

### Conceptual framework

Studies have shown that supportive care programs using a case management approach can reduce readmission rates [42] and enhance quality of life [43]. Results from analyzing 96 sets of case notes of home visits to hospice patients showed that pain and edema can be quite well managed through palliative home care services, but breathlessness less so. Patients also experienced a number of social and psychological issues, such as role change, guilt, and anger, and palliative care proved helpful in reducing the intensity of these symptoms [29].

This intervention introduces a comprehensive Home-based Palliative HF Program (HPHP) to post-discharge patients with ESHF. The HPHP is built on two main conceptual guides: the recommended six principles for palliative HF care [44] and the four-Cs transitional care model. The six principles are as follows: 1) there is case management with coordination of care, communication and periodic review of treatment goals, and a symptom control plan with patient and family; 2) there are opportunities to discuss end-of-life issues; 3) a multidisciplinary approach is adopted; 4) there is a need for staff development, including the art of communication, for cardiovascular and palliative care; 5) topics for discussion of end-of-life issues include advanced directives, preference for treatment plan, and periodic re-evaluation of preference and treatment goals; 6) resources are provided that support an integrated model of HF palliative care [44].

A transitional care model embracing the preceding six principles will be adopted to guide the intervention design of this study. This study took reference of the transitional care model structure built by Naylor [45] and Coleman [46], which includes interfacing the pre-discharge phase with the post-discharge phase, continued with planned, proactive, and sustained follow-up for the post-discharged patients [42]. The design of the transitional care model in this study shares the essence of transitional care proposed by Naylor and Coleman to ensure post-discharge healthcare continuity and to avoid preventable readmissions [39, 45–47] but differs in the content by introducing the principles of HF palliative care as mentioned above. The key features in the transitional model of care to be used in this study are known as the four Cs, and were proposed by Wong et al. [42, 43, 48–50]. The four Cs refer to comprehensiveness, continuity, coordination, and collaboration. Being comprehensive means that the multidisciplinary team, together with the case manager, will conduct a holistic assessment of a patient’s condition and assume responsibility for anticipating the patient’s needs and facilitating the transition to home. Continuity of care is ensured by timely, proactive, and sustained follow-up on a regular basis. Coordination refers to the nurse case manager facilitating the communication with physicians, social workers, and other healthcare team members to respond to patients’ needs when necessary. Collaboration occurs not only among healthcare team members, but also between the provider and the patient/family. The patient/family needs to be involved as a partner, an active agent of care [42, 50].

